### Intervention

#### Get.ON mood enhancer prevention

The GET.ON Mood Enhancer Prevention training consists of six lessons. Participants are advised to do two lessons a week but at least one. Consequently, the training lasts 3 to 6 weeks. However, participants are not excluded from the intervention if they do not manage to complete one lesson a week. Lessons consist of text, exercises, and testimonials. Each lesson includes interactive elements such as audio and video clips. Audio sequences introduce relaxation exercises, whereas video clips are used to explain theoretical frameworks, such as the concept of behavioural activation, in a user-friendly way. A strong focus lies on transfer tasks (homework assignments) to integrate newly acquired strategies and techniques into daily life. As an optional component, participants can choose to receive a set of about 42 standardised text-messages supporting them to integrate the learned techniques into their everyday life. An example of such a text-message would be “Everyone has his own strategies to vanquish the inner temptation. What helps you?” In the beginning of each subsequent lesson, participants are invited to reflect on their experiences with the newly acquired skills. The contents are adaptively tailored to the specific needs of the individual participant by continuously asking participants to respond by choosing among various response options. Subsequent content is then tailored to the participant’s response. For example, participants are asked whether to work on an elective module or not and if so they can choose which module they want to work on.

GET.ON Mood Enhancer Prevention is based on elements from behaviour therapy (BT) [39] and problem-solving therapy (PST) [40]. These therapeutic elements are often found in psychological treatments for subthreshold depression [41]. Interventions using BT and the combination of BT and PST have been shown to effectively prevent the onset of major depressive disorder (i.e. [42,43]). In BT, a strong focus rests on daily pleasurable activity scheduling that is integrated in each lesson (Additional file 1: Screenshots of the GET.ON Mood Enhancer Prevention intervention page 3). The PST elements implemented in GET.ON Mood Enhancer Prevention have been used in various web-based interventions, such as the Dutch web-based “Alles onder Controle” course, which has been shown to be effective in reducing depressive symptomatology across several randomised controlled trials [44,45]. In the current study, PST consists of three steps. First, participants make a list of things that matter most to them in their lives. Second, participants list all their problems and worries and divide them into ‘manageable’ and ‘unmanageable’. Finally, they are invited to think about activities on how to solve the manageable problems. The main focus in problem-solving therapy is to tackle those problems that are manageable by means of a six-step procedure: (1) defining the problem, (2) defining the target state, (3) brainstorming about possible solutions and choosing the best one, (4) making a plan how to implement this solution, (5) actually putting the solution into practice, and (6) evaluating the outcome. Finally, participants make a plan for the future on how they are going to accomplish their goals and those things that are most important to them in their lives (Additional file 1 page 2). In addition to the BT and PST elements, in the last three lessons participants are offered three elective modules targeting sleep hygiene, relaxation techniques, and dealing with worrying thoughts, respectively.

During the training, participants are supported by an online-trainer. The total time a trainer spends on a participant is approximately two hours. Trained and supervised graduate students and health care professionals will provide guidance. Participants will communicate with their trainer trough the internal messaging function of the system on which GET.ON Mood Enhancer Prevention is implemented. The guidance provided by the trainers focus on supporting participants to work through the exercises.

#### Psychoeducational-only condition

The psychoeducational intervention is also web-based and it is implemented on the same platform as GET.ON Mood Enhancer Prevention. Psychoeducational interventions have been shown to be effective in reducing depressive symptoms [46]. In the current study, the psychoeducational intervention is based on the German S3-Guideline/National Disease Management Guideline Unipolar Depression [47]. It informs participants about the nature and evidence-based treatments of depression including information about symptoms and sources of help. They can go through the material as often as they want to. In this study, the psychoeducational intervention does neither require participants to do explicit homework assignments nor is any support by a trainer or other mental health care specialist offered to participants.

### Sample size calculation

We assume an absolute risk reduction of at least 10% for the incidence of major depressive disorder (MDD) between intervention and control group as clinically relevant. Based on previous studies evaluating interventions directed at the prevention of MDD, we expect a mean incidence of MDD in the control group of 25% within the 12-months follow-up period [48-50]. Based on a power of 80%, an alpha of 0.05, a relative risk reduction of 40%, and an attrition rate of 20%, we will need 406 participants to demonstrate an absolute risk reduction of 10% between the groups using log rank survival analyses (calculated using PASS 12).

### Outcome measurements

For an overview of assessment at baseline, post-treatment, 6-and 12-month follow-up see Table 1.

**Table 1 T1:** Overview of outcome measurements

		**Time of measurement**			
**Instrument**	**Aim**	**T0 (Baseline)**	**T1 (Post-test, 6 weeks)**	**T2 (6-month follow-up)**	**T3 (12-month follow-up)**
**Other questions**	Socio-demographics	x			
**SCID** (DSM-IV section for mood disorders)	Diagnostic interview	x		x	x
**CES-D**	Depressive symptom severity	x	x	x	x
**EuroQol**	Quality of life	x	x	x	x
**SF-12**	Subjective functioning/Quality of life	x	x	x	x
**TiC-P**	Health care service utilisation and productivity losses	x		x	x
**HADS-A**	Anxiety symptoms	x	x	x	x
**SPSI-R**	Problem-solving skills	x	x	x	x
**BADS-SF**	Behavioural activation	x	x	x	x
**Pearlin Mastery Scale**	Internal locus of control	x	x	x	x
**PSWQ** (Ultra-brief)	Worrying thoughts	x	x	x	x
**ISI**	Insomnia Severity	x	x	x	x
**CEQ**	Patient expectancy/treatment credibility	x	x		
**ATSPPH-SF**	Attitudes toward seeking professional psychological help	x	x	x	x
**Course evaluation**	Participants’ satisfaction with the GET.ON Mood Enhancer Prevention training		x		
**INEP**	Side-effects of psychotherapy		x	x	

#### Primary outcome

The primary outcome is time to onset of MDD within a 12-months follow-up period. Major depressive disorder will be assessed according to DSM-IV criteria as assessed by the telephone-administered Structured Clinical Interview for DSM-IV (SCID) at 6 and 12 months [37,38]. The inter-rater agreement of the Axis I disorders is moderate to excellent [51]. The agreement between face-to-face and telephone SCID interviews as indicated by the kappa coefficient is considered to be excellent [52]. Time to onset of MDD will be assessed using life charts. Life events are recalled by using a calendar method after which the presence of depressive symptoms at each month during the follow-up period is determined. SCIDs will be conducted by trained psychologists who are blind to treatment condition. The interviews will be recorded to examine inter-rater reliability. Disagreement shall be solved by discussion and the agreed rating will be used for analysis. If this is not possible, the assessment will be rated by an experienced psychotherapist (gold standard) and this rating will be used for analysis.

### Secondary outcomes

Self-report data will be collected using a secured online-based assessment system (AES, 256-bit encrypted).

#### Depressive symptomatology

The depressive symptom level will be assessed with the German version of the Center for Epidemiological Studies Depression Scale (CES-D) [53]. The CES-D is a self-report scale and consists of 20 items, each scored 0–3, covering four domains: depressive affect, somatic complaints/activity inhibition, positive affect, and interpersonal difficulties. The total score ranges from 0–60, with a higher score indicating more severe depressive symptoms. A cut-off of 16 is usually regarded as indicating clinically relevant depressive symptom severity. The reliability of the CES-D has been shown to be excellent (internal consistency of Cronbach’s α = .89) [53].

#### Quality of life

Health-related quality of life will be assessed with two multidimensional generic measures, i.e., the EuroQol [54] and the SF-12v1 Health Survey [55]. The EuroQol entails the EQ-5D and a visual analogue scale. The EQ-5D consists of five items covering five dimensions (mobility, self-care, usual activities, pain/discomfort, and anxiety/depression), each of which is rated as causing ‘no problems’, ‘some problems’, or ‘extreme problems’. The SF-12v1 has 12 items covering eight health domains (physical functioning, role functioning (physical and emotional), bodily pain, general health, vitality, social functioning, and mental health). The SF-12 generates two summary scores, the physical and mental health summary scores, respectively.

#### Anxiety

Anxiety will be measured with the German version of the anxiety subscale of the Hospital Anxiety and Depression Scale (HADS-A) [56,57]. The anxiety subscale consists of seven questions and each is scored from 0-3 meaning that the total scores ranges from 0-21 where a score between 0-7 indicates no anxiety, between 8 and 10 possible anxiety, and above 11 or 12 a clinical anxiety disorder. Psychometric properties are well established (Cronbach’s α ranging from .63-.93) [58].

#### Problem-solving skills

Problem-solving ability (i.e., generalised appraisal, beliefs, expectancies, and emotional responses) will be measured with two subscales of the Social Problem-Solving Inventory-Revised (SPSI-R). The positive problem orientation (PPO) subscale will represent a constructive dimension whereas the negative problem orientation (NPO) subscale is viewed as a dysfunctional dimension. Both subscales have displayed strong psychometric properties in former studies (Cronbach’s α = .76; .83) [59].

#### Behavioural activation

Participants’ activation towards goals/values and pleasant activities and avoidance behaviours will be measured with the BADS-Short Form (BADS-SF) [60]. The BADS-SF entails 9 items comprising two subscales (activation and avoidance). The items are rated on a 7-point Likert-type scale. Higher scores indicate that the individual scores high on the area of interest. The BADS-SF shows good psychometric properties (Cronbach’s α = .82) [60].

#### Mastery (internal locus of control)

Internal locus of control will be measured with the Pearlin Mastery Scale [61]. The Pearlin Mastery Scale consists of 7 items and each is rated on a 4-point Likert scale. The higher the score, the more the individual perceives having control over situations (internal mastery). A lower score points to external mastery meaning that the individual generally has the feeling that things are out of his or her control. The psychometric properties of this scale are well established [61].

#### Worrying

Worrying will be assessed with the ultra-brief version of the Penn State Worry Questionnaire (PSWQ) [62]. The ultra-brief version consists of 3 items stemming from the standard version, with each item being rated on a 7-point scale. The total score range from 0-18 with higher scores indicating more worry. The ultra-brief version shows similar psychometric properties compared to the standard version (Cronbach’s α = .85) [62].

#### Insomnia severity

Insomnia severity will be measured because evidence shows that treating sleep problems can ease depressive symptoms. Insomnia severity will be assessed with the Insomnia Severity Index (ISI) [63]. The ISI measures the nature, severity, and impact of insomnia. It consists of 7 items; each is rated on a 5-point Likert scale resulting in a total score ranging from 0 to 28. Higher scores indicate more severe insomnia. The ISI is a valid and reliable instrument to detect cases of insomnia in a population-based sample. The internal consistency is excellent (Cronbach’ α = .90) [64].

#### Treatment credibility/patient expectancy

Training credibility and participants’ expectancy for improvement will be measured with the credibility and expectation questionnaire (CEQ). The CEQ consists of 6 items, which are rated on a 9- or sometimes 10-point Likert scale. The psychometric properties of the instrument are well established (Cronbach’s α = .86) [65].

#### Attitudes toward seeking professional psychological help

The influence of attitudes on mental health care service utilisation will be measured with the Attitudes Toward Seeking Professional Psychological Help Scale-SF (ATSPPH-SF) [66]. The ATSPPH-SF consists of 10 items that are rated on a 4-point Likert scale yielding a total score ranging from 0-30. High scores indicate positive treatment attitudes. The instrument showed good psychometric properties in a previous study. The internal consistency ranges from .82 to .84 [67].

#### Course evaluation

User satisfaction will be measured with a self-designed questionnaire that is based on the “Satisfaction with Psychotherapy” Questionnaire (ZUF-8, [68]), the German version of the Client Satisfaction Questionnaire (CSQ-8, [69]). This self-report measure consists of 8 items measuring the global client satisfaction with the web-based training. Previous research indicated a high internal consistency (Cronbach’s α = .91) [70].

#### Side-effects of psychotherapy

Side-effects of psychotherapy will be measured with the side-effects of psychotherapy inventory (INEP) [71]. The INEP consists of 15 items assessing any changes participants experienced after the completing of the web-based training in their social and/or work environment that they directly relate to their participation in the web-based training.

#### Key economic outcomes

##### Clinical endpoints

In the cost-effectiveness analyses, the main outcome will be depression-free years gained. Depression-free years will be assessed by calculating the difference in follow-up lengths and the duration of any major depressive episode (i.e. period of time in weeks that a person met DSM-IV criteria). In the cost-utility analysis, quality-adjusted life years (QALYs) will be the clinical endpoint. QALYs will be obtained from the EQ-5D (EuroQol) and SF-6D (SF-12v1). The EuroQol will be used because it is a widely applied quality of life instrument and its reliability and validity is well established [54]. Theoretically, the EQ-5D generates 243 different health states. Index scores for each of these health states are available for various countries with “perfect health” and “death” being assigned values of 1 and 0, respectively. In this study, the index scores derived from a large general population sample in the UK will be used [72]. For the sensitivity analysis, the German index scores [73] will be applied. The EQ-5D, however, might suffer from a ceiling effect meaning that a large number of respondents suffering from mild manifestations of depressive symptoms report no problems. Hence, the SF-6D will also be used because it might be the more appropriate measure for milder conditions, i.e., subthreshold depression [74]. The SF-6D contains 6 dimensions (each with between 2 and 5 levels) and includes 7 items of the SF-12. The SF-6D generates 7500 different health states. Utility values will be derived using Brazier’s algorithm [75,76].

##### Costs

Direct medical (i.e. health care service utilisation) and direct non-medical costs (i.e. all costs not directly related to medical services such as transportation) are measured with the TiC-P, which is a self-report questionnaire [77]. Indirect non-medical cost stemming from production losses due to absenteeism and presenteeism will be assessed with specific modules of the TiC-P. A catalogue of unit costs (i.e. inpatient, outpatient and rehabilitative services) and evaluation standards of the Association of Statutory Health Insurance Physicians [78] will be used to calculate the total care costs on an individual basis [79].

### Statistical analyses

#### Clinical efficacy

The study will be conducted in agreement with the CONSORT statement. Differences in the time to onset of MDD will be analysed in a proportional log rank survival analysis over a follow-up period of 12 months after baseline. Time to onset will be the dependent variable in the survival analyses. Analyses will be done based on the intention-to-treat (ITT) principle. In addition, per-protocol analyses will be performed. For participants who are lost from the trial, available measurements will be used and then censored at the time of their last observation. Participants who miss the assessment at 6-months follow-up, but are then assessed at 12-months follow-up, will be asked about their current and past symptoms according to SCID diagnostic criteria since the diagnostic interview at baseline. This will enable us to assess the time to onset of a depressive episode and thus to censoring. One-sided tests will be used for testing unidirectional and two-sided tests for testing bidirectional hypotheses. For all analyses statistical significance will be set at p < .05. We will calculate the number needed-to-be-treated (NNT) with GET.ON Mood Enhancer Prevention to prevent one case of MDD as compared to the control group to estimate the clinical effect size.

In secondary analyses, hierarchical linear modelling will be used to assess differences in secondary outcomes, such as depressive symptom severity, anxiety, and quality of life. We will also explore the proportion of major depressive episodes in the intervention and control group by follow-up. For all mixed-model analyses, Cohen’s d will be calculated by standardising the differences between baseline and follow-up scores by the pooled standard deviation of baseline scores.

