### Inclusion and exclusion criteria

We will include adults (a) age 18 and above who (b) suffer from subthreshold depression (Centre for Epidemiological Studies Depression Scale (CES-D) ≥ 16) but do not meet DSM-IV criteria for a major depressive episode, (c) have Internet access, and (d) are willing to give informed consent. We will exclude subjects who (a) meet DSM-IV criteria for (a) current major depressive episode, (b) a bipolar disorder, or (c) a psychotic disorder. Additional exclusion criteria are: (d) a history of a major depressive disorder in the past six months (based on Kupfer [35]), (e) currently receiving psychotherapy for any kind of mental health problems, (f) being on a waiting list for psychotherapy, (g) receiving psychotherapy in the past six months, and (h) showing a notable suicidal risk, as indicated through a score greater 1 in the Beck Depression Inventory (BDI) Item 9 (“I feel I would be better off dead”).

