#### Economic analyses

It will be checked whether baseline differences exist between the intervention and control group. If necessary, statistical techniques will be used to correct for baseline differences [80]. In the cost-effectiveness analyses, the incremental cost-effectiveness ratio (ICER) will be stated as costs per depression-free years gained, whereas the ICER in the cost-utility analyses will represent the costs per quality-adjusted life year (QALY) gained. Bootstrapping will be used to test the robustness of the ICERs and quantify the uncertainty around the ratios that will be graphically represented on a cost-effectiveness plane. The bootstrapped ICERs will also be shown in a cost-effective acceptability curve disclosing the probability that GET.ON Mood Enhancer Prevention is cost-effective for a wide range of willingness-to-pay ceilings [81]. To test the robustness of the base-case findings, a multi-way sensitivity analysis will be done. An incremental net benefit regression analysis will be performed to ascertain which sub-groups benefit more from the intervention in terms of superior cost-effectiveness.

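### Baseline adjustment in the economic analysis should be unconditional, and the primary survival method should be named, preferably with baseline CES-D as a prespecified covariate

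*Protocol article*

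**What the plan says.** **Economic evaluation (Protocol article, Economic analyses).** The arms are first compared at baseline. Then: "If necessary, statistical techniques will be used to correct for baseline differences". A literature reference is attached, but the text gives no criterion for necessity, no variable and no technique. Table 1 lists the EuroQol, SF-12 and TiC-P at T0, so baseline utility and baseline costs are collected.

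**Primary outcome (Protocol article, Clinical efficacy).** "Differences in the time to onset of MDD will be analysed in a proportional log rank survival analysis", over 12 months. No covariate or stratum is named. The effect measure announced for this outcome is the number needed to treat; no hazard ratio is mentioned. On the level and direction of tests: "For all analyses statistical significance will be set at p < .05" and "One-sided tests will be used for testing unidirectional and two-sided tests for testing bidirectional hypotheses".

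**Related text.** The sample size section relies on log-rank analyses, with "we expect a mean incidence of MDD in the control group of 25% within the 12-months follow-up period" and "a relative risk reduction of 40%, and an attrition rate of 20%, we will need 406 participants". The randomisation section describes blocks of two and states no stratification factor. The CES-D is measured at baseline in everyone. The eligibility section excludes "a history of a major depressive disorder in the past six months", so people with older episodes may enter.

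**The concern.** The two parts share one theme, the use of baseline data, but they are separate issues.

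**Economic part.** Under a check-then-correct rule the data choose the estimator. Randomisation is unstratified as far as the article states, so balance on utility and cost is left to chance. Baseline utility can be expected to predict follow-up QALYs, and baseline cost to predict follow-up cost, whether or not a difference is flagged. Where none is flagged, the chance imbalance passes into the incremental QALYs and costs, and the variance that the baseline values explain stays in the bootstrap distribution. An unstated trigger also lets the adjustment be decided after the data are seen.

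**Primary part.** The label joins two different things. A log-rank test takes no covariates and gives no effect estimate; a proportional hazards model does both. The reader cannot tell which is primary. If it is the plain log-rank test, a baseline symptom score held on every participant goes unused in the main comparison, and any power it could add is forgone.

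**Working it through.** **1. Economic part: size of an uncorrected imbalance**

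Inputs: 203 per arm (406/2, from the article). Assumptions, because the article gives none: utility SD 0.12 to 0.20, correlation 0.6 between baseline utility and QALYs, equal SDs for the two.

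- SE of a chance baseline difference = SD × √(2/203) = SD × 0.0993, which is 0.012 (SD 0.12) to 0.020 (SD 0.20).
- Shift in the QALY difference = slope × imbalance. With equal SDs the slope equals the correlation, 0.6. A one-SE imbalance gives 0.6 × 0.012 = 0.007 to 0.6 × 0.020 = 0.012.
- If the check were a 5% significance test (assumption), differences up to 1.96 SE would go unflagged: 0.023 to 0.039, with a QALY shift of up to 0.014 to 0.023. Under randomisation such a test stays silent on any given variable in about 95% of trials.
- Precision: adjustment removes r² = 0.36 of the QALY variance, so the SE falls by the factor √(1 − 0.36) = 0.8, flagged difference or not.

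No power figure can be given here: the article states no target, SD or correlation for the economic outcomes.

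**2. Primary part: base power**

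Inputs from the article: 25% control risk, 10-point reduction (so 15%), alpha 0.05, power 80%, attrition 20%, N = 406.

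- Hazard ratio = ln 0.85 / ln 0.75 = 0.565.
- The article's own figure first. Schoenfeld, two-sided: 4 × (1.960 + 0.842)² / (ln 0.565)² = 97 events; 97/0.20 = 485; 485/0.8 = 607. One-sided: 76 events, 380, then 475. The stated 406 is not reproduced with 20% attrition on either side. That is a separate sample-size matter and serves here only to fix the base.
- With participants kept until censoring, as the article plans, and 20% exponential loss over the year, event probabilities are 0.225 and 0.135. Expected events = 203 × (0.225 + 0.135) = about 73. Power = Φ(√73.1 / 2 × 0.571 − 1.96) = Φ(0.48) = 68% two-sided; with 1.645 in place of 1.96 it is 79%.

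**3. Primary part: what adjustment adds**

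Simulation: 8,000 trials per row, 203 per arm, marginal risks held at 25% and 15%, 20% exponential loss, one normally distributed baseline covariate. The covariate strength is an assumption; the article gives none. Unadjusted log-rank test against a Cox model with arm and covariate (Wald test):

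| Covariate HR per SD | Two-sided: log-rank | Two-sided: Cox | One-sided: log-rank | One-sided: Cox |
|---|---|---|---|---|
| 1.0 | 67.4% | 66.6% | 77.3% | 77.0% |
| 1.3 | 67.7% | 67.8% | 78.3% | 78.4% |
| 1.5 | 67.6% | 68.5% | 78.3% | 79.6% |
| 2.0 | 67.8% | 71.9% | 78.2% | 81.6% |
| 2.5 | 67.7% | 75.5% | 77.9% | 84.3% |

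Two-sided change: −0.8, +0.1, +0.9, +4.1 and +7.8 points. The comparison sets a score test against a Wald test, so part of the small loss in the first row may come from the form of the test.

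**The case against.** An unadjusted log-rank test is valid in a randomised trial and agrees with the basis on which this one was sized. A covariate list is what a condensed article commonly leaves to the full protocol or analysis plan, and nothing in the text forbids adjustment. All of this stands, and it is why the primary part is a recommendation and not a fault.

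The power gain depends wholly on a prognostic strength that the article does not give. Entry requires a CES-D of at least 16 and no current major depressive episode, which may narrow the spread of the score. This stands too: a gain near zero is possible. Nor is adjustment free. The Cox hazard ratio becomes conditional on the covariate. In the simulation the same marginal risks correspond to a conditional hazard ratio of 0.546 at 2.0 per SD and 0.529 at 2.5, against 0.565 with no covariate effect. A covariate that does not predict onset may cost just under one point of power.

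On the economic side, the cited reference may set out a technique or trigger, and it cannot be seen here. A reference could supply the technique, but the adjustment would still be conditional, and the conditioning is the weakness. It is also fair that the main cost-effectiveness outcome, depression-free years, has no varying baseline value, since everyone enters without a current episode. On the effect side the point therefore reaches only the cost-utility analysis; costs enter both ratios. No threshold in the article says whether a shift of 0.007 to 0.012 QALYs would change a decision.

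A reader might also infer that MDD history is a ready covariate. The article names older episodes only through an exclusion window and lists the SCID simply as a diagnostic interview, so this needs confirming.

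**Conclusion.** The economic rule is fixed badly: adjustment conditional on an observed difference, with no stated trigger, where unconditional adjustment uses data already collected. Under the assumed SDs and correlation, the effect is a shift of about 0.007 to 0.012 QALYs per standard error of chance imbalance, and a standard error about 20% larger than adjustment would leave it if expressed against the unadjusted one.

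The primary method is named ambiguously and should be settled. Adding baseline CES-D is a sensible improvement, worth anything from nothing to about 8 points of two-sided power over the assumed range, and about 1 to 4 points for hazard ratios of 1.5 to 2.0 per SD.

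Three stronger readings are not supported. The unadjusted primary test is not an error. It cannot be said to cost a definite amount of power, because no prognostic strength is documented. The economic rule has no bearing on the power of the primary test. Nor are baseline data ignored throughout, since the secondary outcomes use hierarchical linear models over repeated measures that include baseline.

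**What to change.** **Economic analyses.** Delete the condition. State that QALYs are always adjusted for baseline utility (from the same instrument, EQ-5D or SF-6D) and costs for baseline TiC-P costs, by regression within each bootstrap replicate.

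**Clinical efficacy.** Name one primary method. Preferably prespecify a Cox model with arm and continuous baseline CES-D, plus history of MDD if the baseline SCID records it. Use Efron's method for ties, since the life charts date onset by month, and report the hazard ratio with its 95% confidence interval, described as conditional on the covariates. Keep the unadjusted log-rank test and Kaplan-Meier curves alongside. If the sponsor prefers the log-rank test as primary, say so plainly and make the Cox model the prespecified effect estimate.

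**Cost.** Wording and a little programming. Utility, costs and CES-D are already collected at baseline; only the MDD history needs confirming. The choice must be made before outcome data are seen by arm.
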